#### 2.7.5. Intervention-Related Outcomes

Motivation for therapy will be measured with the Portuguese version of the Client Motivation for Therapy Scale (CMTS; psychometric studies ongoing) [50]. The CMTS comprises 24 items (e.g., “Because I would like to make changes to my current situation”) rated on a seven-point response scale ranging from 1 (not true at all) to 7 (totally true). Higher scores suggest higher motivation for therapy. 

The therapeutic relationship will be assessed with the Portuguese version of the Working Alliance Inventory—Short revised (WAI-SR) [51], a 12-item instrument with a five-point response scale ranging from 1 (rarely or never) to 5 (always). Higher scores indicate better therapeutic alliance. The Portuguese version of WAI-SR is a reliable measure and has good levels of internal consistency (Cronbach’s alpha = 0.85).

Acceptability, satisfaction, and usability of the blended treatment will be measured through specific questions developed by the researchers (e.g., satisfaction with the program, usefulness, acceptability, demandingness, recruitment rate, dropout rate, web system data).

The feasibility of the program will be assessed through website utilization (e.g., number of logins, average visit length, total time spent on the website, number of exercises completed) and dropout rate.

#### 2.7.6. Economic Evaluation

Cost-effectiveness will be assessed with an adapted version of the Treatment Inventory Cost in Psychiatric Patients (TiC-P) [52]. This instrument measures medical costs and indirect nonmedical costs, through the assessment of the participant’s healthcare use in the last three months (i.e., the number of contacts with healthcare providers), productivity losses (i.e., the number of days of absence from work due to illness), and efficiency at work in the last four weeks.

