## 1. Introduction

Postpartum depression (PPD) is a serious clinical condition affecting approximately 13% of Portuguese women after childbirth [1]. When left untreated, PPD poses adverse and persistent consequences for the entire family system. It affects the woman’s health (e.g., increased tiredness [2], decreased quality of life [3]) and mother–child interaction (e.g., mother-child bonding, lower parenting self-efficacy) [3,4]. Moreover, it can have consequences for the infant’s development (e.g., infant sleep patterns, emotional development) [3] and for the entire family environment, including the couple’s relationship [5].

Despite the existence of effective treatments (e.g., cognitive–behavioral therapy [CBT]) [6], few women with PPD seek professional help [7]. A Portuguese study revealed that only 13.6% of women with depressive symptoms during the perinatal period sought professional help to address their emotional difficulties [8]. Time and financial constraints and struggles with transportation and childcare issues are some of the structural barriers to seeking professional help reported by postpartum women [9,10], suggesting the need for new delivery formats to improve women’s access to evidence-based PPD interventions.

E-mental health tools are an innovative form of treatment delivery that use digital technology, including web-based technology, in the mental health field [11]. These tools can overcome PPD treatment uptake barriers given their reduced costs, flexibility, and improved accessibility [12]. Women in the postpartum period already use the internet frequently to search for information about PPD [10]. Moreover, e-mental health tools have been perceived as acceptable and useful among Portuguese women in the perinatal period, particularly among those women presenting clinically relevant depressive symptoms [13].

Existing web-based interventions for PPD treatment based on CBT have proven to be effective in the reduction of postpartum depressive symptoms [14,15,16]. Interventions such as MomMoodBooster [17], NetMums [18], and Mom-Net [19] have shown promising results not only in reducing postpartum depressive symptoms but also in improving self-efficacy, marital relationship, and mother–child bonding.

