## 2. Materials and Methods

### 2.1. Study Design

This study will be a two-arm, noninferiority randomized controlled trial (RCT) comparing blended CBT intervention for PPD (Blended Be a Mom) to the usual treatment that women receive to treat PPD in primary healthcare centers (treatment as usual; TAU). Participants in both the Blended Be a Mom and TAU conditions will complete baseline, postintervention, and follow-up (three and six months postintervention) assessments through a link sent by email that gives access to the survey.

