### 2.6. Interventions

#### 2.6.1. Blended Intervention

The blended protocol will be developed based on existing evidence-based CBT interventions for PPD delivered both face-to-face (e.g., [36]) and online (e.g., [37]). The final blended CBT intervention protocol for PPD (Blended Be a Mom) will be developed by the research team and reviewed and approved by a panel of researchers with clinical expertise in the area of PPD. A pilot study with women with a clinical diagnosis of PPD will be conducted prior to the RCT, to assess the acceptability and feasibility of the structure and content of the blended intervention, and to gather preliminary evidence of its clinical efficacy (noncontrolled). Appropriate adjustments to the blended intervention protocol will be done accordingly.

The Blended Be a Mom intervention will integrate 7 face-to-face CBT sessions that are weekly alternated with 6 online sessions over a period of 13 weeks. The online part of the blended intervention will be adapted from the Be a Mom program. Both face-to-face and online sessions will be designed according to CBT principles: problem-oriented, structured, time-limited, educative, and promoting the active participation of the patient [38]. The content of sessions will include psychoeducation, cognitive strategies for negative thoughts, behavioral activation, and relapse prevention (more detailed information is presented in Figure 2). The intervention will also include the utilization of a mobile phone application to conduct ecological momentary assessment, a method to collect information in real time and in the natural environment of participants, over a period of time [39].

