### 2.8. Sample Size and Statistical Analyses

The sample size for this study was determined based on power analysis (G*Power). A sample of 45 women per condition is required to detect medium effects in comparison analyses, considering the primary outcome. Considering an expected dropout rate of 20%, we plan to recruit a sample of at least 110 participants (55 per condition) to account for attrition effects.

Statistical analyses to examine the efficacy of the program will be conducted following the intention-to-treat (ITT) and per-protocol (PP) principles in accordance with the CONSORT recommendations [53]. ITT analyses allow us to examine data from all randomized participants, even those with missing values on outcome measures. In contrast, PP analysis includes only participants who followed the assigned treatment protocol. Statistical analyses will be performed using the Statistical Package for the Social Sciences (SPSS, Version 25.0; IBM SPSS) and the Mplus program (Version 7). Linear mixed models will be conducted to determine the effects of the intervention over time (time × group interaction effects) on primary and secondary outcomes and changes in psychological competences. Other appropriate statistical analyses such as two-wave latent change score models, reliable change index, Chi-square tests, and within-group effect sizes will be performed, as well as mediator and moderator analysis. Preliminary cost-effectiveness analysis will be conducted from a healthcare cost perspective and a societal perspective, comparing the differences between the intervention and control group on the outcomes, with the differences in the costs generated. The contribution of a health economics expert will be required.

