**Figure 2 ijerph-17-08631-f002:**
[figure not shown]
Blended Be a Mom—structure and content of sessions.

**Table 1 ijerph-17-08631-t001:** Study variables and assessment points.

Variables	Baseline [T0]	Postintervention [T1]	Follow-Up [T2]	Follow-Up [T3]
Sociodemographic, clinical and obstetric information	x			
Depressive symptoms	x	x	x	x
Anxiety symptoms	x	x	x	x
Fatigue	x	x	x	x
Quality of life	x	x	x	x
Marital satisfaction	x	x	x	x
Maternal self-efficacy	x	x	x	x
Mother–child bonding	x	x	x	x
Self-compassion	x	x		
Emotion regulation	x	x		
Psychological flexibility	x	x		
Motivation for therapy	x	x		
Therapeutic relationship		x		
Acceptability, satisfaction, and usability		x		
Economic evaluation	x	x

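### Table 1 stops cost collection at T1 while outcomes run to T3, so about two thirds of the observation period has no TiC-P cost data and the cost-effectiveness analysis cannot be matched to the follow-up effects

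*Protocol article*

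**What the plan says.** Section 2.7.6 of the protocol article names one cost instrument, an adapted TiC-P. It collects healthcare use "through the assessment of the participant’s healthcare use in the last three months", days of absence from work, and efficiency at work over four weeks.

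The last row of Table 1 reads "Economic evaluation x x". The row for the primary outcome reads "Depressive symptoms x x x x", and quality of life (EQ-5D) is also marked at all four points.

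The timing follows from two sections. Section 2.6.1 describes "7 face-to-face CBT sessions that are weekly alternated with 6 online sessions over a period of 13 weeks". Section 2.1 sets "follow-up (three and six months postintervention) assessments", completed in both arms through an emailed survey link.

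Section 2.8 plans a preliminary cost-effectiveness analysis from healthcare and societal perspectives, "comparing the differences between the intervention and control group on the outcomes, with the differences in the costs generated". It gives no time horizon and says that a health economics expert will be needed. The Discussion expects the blended intervention to match TAU on long-term effects and says that cost-effectiveness will be considered as well.

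**The concern.** A cost-effectiveness comparison needs costs and effects over the same period. Here the effects are followed for six months after the intervention, while the cost instrument is given for the last time when the intervention ends. The T0 administration looks back to before randomisation, so T1 is the only one that describes costs incurred under the allocated treatment.

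The weeks after T1 may matter, and not equally in both arms. Section 2.6.1 says that some blended participants will leave the intervention and be referred to other mental health services; that care may continue past T1. Section 2.6.2 gives TAU no fixed length, so it may continue past week 13. For TAU the article promises information on type and duration of therapy, but that is not a record of all healthcare use or of lost productivity.

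The trial is a noninferiority trial that expects similar effects, and the article presents lower cost as a main reason to adopt the blended format. The cost comparison therefore carries weight although it is secondary. Costs not collected at T2 and T3 cannot be recovered by a later analysis plan.

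**Working it through.** **Inputs**
- Intervention: 7 face-to-face and 6 online weekly sessions (section 2.6.1).
- Follow-up: three and six months after the intervention (section 2.1).
- Recall: three months for healthcare use, four weeks for efficiency at work (section 2.7.6). The sentence does not make clear which period applies to days of absence, so these are left out of the arithmetic.
- Cost collection: T0 and T1. Depressive symptoms and EQ-5D: T0 to T3 (Table 1).

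**The plan's own figure.** 7 + 6 = 13 weekly sessions, which reproduces the stated 13 weeks.

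**Observation period.** Taking six months as 26 weeks, 13 + 26 = 39 weeks from the start of treatment to T3.

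**Healthcare use covered as scheduled.** At 4.345 weeks per month, three months is 3 × 4.345 = 13.0 weeks. The T1 recall thus spans the 13 treatment weeks. The T0 recall lies before randomisation and adds nothing afterwards.

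**Share without TiC-P data on healthcare use**

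| Convention for six months | Uncovered / total | Share |
|---|---|---|
| 26 weeks | 26 / 39 | 66.7% |
| 24 weeks | 24 / 37 | 64.9% |
| Calendar months | 6 / 9 | 66.7% |

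**Efficiency at work as scheduled.** The T1 recall covers 4 / 13 = 31% of the treatment period and 4 / 39 = 10% of the whole period.

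**Coverage if collection is extended**

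| Administrations after T0 | Healthcare use | Efficiency at work (four-week recall) |
|---|---|---|
| T1 (as scheduled) | 13 / 39 = 33% | 4 / 39 = 10% |
| T1 and T3 | 26 / 39 = 67% | 8 / 39 = 21% |
| T1, T2 and T3 | 39 / 39 = 100% | 12 / 39 = 31% |

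Adding T3 alone would leave T1–T2 uncovered. Adding both closes the gap for healthcare use but not for efficiency at work.

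**The case against.** The strongest reply is that no horizon beyond T1 was promised. The analysis is called preliminary, an expert is still to contribute, and a horizon is commonly set in a full protocol or analysis plan that is not shown. Table 1 fits an analysis that stops at T1: three months of healthcare use set against EPDS and EQ-5D at the same visit, with no mismatch inside that analysis. This stands in part. The article does not contradict itself, and a T0–T1 analysis of healthcare costs would be coherent. But the article does not say that this is the plan, and the absence of cost data after T1 is a matter of collection, which no analysis plan can repair.

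A second reply is that the economic row is the last line of the extracted text and lacks the trailing empty cells of other rows with two marks. Blanks stripped at the end of the file are the likeliest reason, and the marks present fall under T0 and T1. The published table should still be checked.

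Three stronger readings are tempting, and the documents do not support them:
- A reader might infer that costs after T1 will be counted as zero, or that T1 costs will be divided by T3 effects. Nothing in section 2.8 says either, so a bias in the estimate is not shown.
- A reader might infer that the societal perspective omits travel and childcare costs that blended care is said to save. The Introduction says "Time and financial constraints and struggles with transportation and childcare issues are some of the structural barriers" to seeking help; that describes barriers, not savings. It mentions travel time savings elsewhere, but no saving on childcare. The items of the adapted TiC-P are not listed, so an omission cannot be established.
- A reader might infer that nothing at all is known about TAU after T1. Section 2.6.2 says that type and duration of therapy will be obtained and does not say that this stops at T1.

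**Conclusion.** The concern holds as a gap in data collection. As Table 1 is scheduled, about 26 of 39 weeks (65% to 67%, depending on how six months is counted) have no TiC-P data on healthcare use, and efficiency at work is observed for about 4 of 39 weeks. Cost differences cannot be matched to the T2 or T3 differences in depressive symptoms, or to EQ-5D over follow-up. Later care may differ by arm; neither the size nor the direction of any such difference can be derived from the article.

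This rests on three assumptions: that the two marks in the economic row belong to T0 and T1; that T1 falls about 13 weeks after the start in both arms, although TAU has no fixed length; and that no other cost source is planned beyond the TiC-P and the TAU therapy record. If the analysis is meant to end at T1, the point reduces to saying so and limiting the conclusions accordingly. The primary efficacy comparison is unaffected.

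**What to change.** Check the economic row against the published table. If it stops at T1, add the TiC-P to the T2 and T3 online surveys in both arms, mark both columns in Table 1, and state the horizon of the cost-effectiveness analysis in section 2.8. This covers healthcare use from baseline to T3. For efficiency at work, either lengthen the recall or state that the four-week windows are samples of the period and how the time between them will be handled.

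The cost is one questionnaire in two surveys already scheduled, with slightly more burden for participants. It has to be done before participants reach T2.

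If collection is not extended, limit the cost-effectiveness analysis to T0–T1 with T1 effects, and draw no conclusion on cost-effectiveness over the follow-up.

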### 2.8. Sample Size and Statistical Analyses

The sample size for this study was determined based on power analysis (G*Power). A sample of 45 women per condition is required to detect medium effects in comparison analyses, considering the primary outcome. Considering an expected dropout rate of 20%, we plan to recruit a sample of at least 110 participants (55 per condition) to account for attrition effects.

Statistical analyses to examine the efficacy of the program will be conducted following the intention-to-treat (ITT) and per-protocol (PP) principles in accordance with the CONSORT recommendations [53]. ITT analyses allow us to examine data from all randomized participants, even those with missing values on outcome measures. In contrast, PP analysis includes only participants who followed the assigned treatment protocol. Statistical analyses will be performed using the Statistical Package for the Social Sciences (SPSS, Version 25.0; IBM SPSS) and the Mplus program (Version 7). Linear mixed models will be conducted to determine the effects of the intervention over time (time × group interaction effects) on primary and secondary outcomes and changes in psychological competences. Other appropriate statistical analyses such as two-wave latent change score models, reliable change index, Chi-square tests, and within-group effect sizes will be performed, as well as mediator and moderator analysis. Preliminary cost-effectiveness analysis will be conducted from a healthcare cost perspective and a societal perspective, comparing the differences between the intervention and control group on the outcomes, with the differences in the costs generated. The contribution of a health economics expert will be required.

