### 2.5. Randomization

After completing the baseline assessment, participants will be randomly assigned (blocked randomization, allocation 1:1) to the intervention (Blended Be a Mom) or the TAU conditions (see Figure 1). Randomization will be conducted by a researcher blind to the assessment procedure and will be performed using a computerized random number generator. Women in both conditions will be informed about their assigned treatment condition. Blinding for treatment conditions will not be possible.

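### At the stated 20% dropout, the minimum of 55 women per condition leaves 44 completers, one below the stated requirement of 45: a minor arithmetic inconsistency

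*Protocol article*

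**What the plan says.** The article's section 2.8 (Sample Size and Statistical Analyses) gives three figures in two consecutive sentences.

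- The requirement: "A sample of 45 women per condition is required to detect medium effects in comparison analyses, considering the primary outcome".
- The loss and the target: "Considering an expected dropout rate of 20%, we plan to recruit a sample of at least 110 participants (55 per condition"). The sentence goes on to say that this number is meant to cover attrition.

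Section 2.5 sets equal allocation ("blocked randomization, allocation 1:1"), so the total divides evenly between the conditions. Section 2.8 then plans both an intention-to-treat analysis, which keeps randomised women whose outcome data are incomplete, and a per-protocol analysis. Linear mixed models are the main method.

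**The concern.** The target is presented as the requirement enlarged for attrition. The reader is therefore entitled to apply the stated dropout to the stated target and recover at least the stated requirement. That check fails by one woman in each condition. All three inputs are explicit, so the mismatch cannot be put down to an unstated assumption.

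What is at stake is the accuracy of a figure that others will copy: the recruitment minimum and the dropout it is said to absorb. The validity of the trial is not at stake.

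**Working it through.** **Inputs, all from section 2.8 except the last:** required after attrition, n = 45 per condition (90 in total); expected dropout, d = 0.20; planned minimum, 55 per condition (110 in total); allocation 1:1 (section 2.5).

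**1. Can the stated figures be reproduced?** The 45 cannot be checked, because the article gives no alpha, sidedness, power or numerical effect size, and does not name the G*Power test. Nothing below depends on it. For the 55, the standard inflation is n / (1 − d):

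- per condition: 45 / 0.80 = 56.25, rounded up to 57;
- on the total: 90 / 0.80 = 112.5, rounded up to 113;
- rounding up within each condition first: 2 × 57 = 114.

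The stated 55 is 2 below 57. The stated 110 is 3 below 113 (3 / 113 = 2.7%) and 4 below 114. This is close, but neither 56.25 nor 112.5 rounds to the stated figure.

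**2. Completers at the stated target.** 55 × 0.80 = 44 per condition and 110 × 0.80 = 88 in total, against 45 and 90. The shortfall is 1 per condition (1 / 45 = 2.2%).

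**3. Dropout that the target does cover.** 1 − 45 / 55 = 0.182, or 18.2%.

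**4. Effect on power.** This needs assumptions that the article does not supply. Take a two-sample t-test, a standardised difference of 0.5 as one reading of a medium effect, and alpha = 0.05. The noncentrality is 0.5 × √(n / 2), with 2n − 2 degrees of freedom.

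| n per condition | Noncentrality | Power, two-sided | Power, one-sided |
|---|---|---|---|
| 45 | 0.5 × √22.5 = 2.372 | 65.0% | 76.1% |
| 44 | 0.5 × √22 = 2.345 | 64.0% | 75.2% |

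The change is about one percentage point either way. Only this difference is of interest here. The power levels depend on the assumed inputs and say nothing about what the sponsor calculated.

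**The case against.** The case for leaving the sentence alone has four parts.

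- **The target is a minimum.** Recruiting 114 women would comply with the plan as written. That is true, but a minimum is the number the plan treats as enough, and at that number the requirement is missed.
- **Expected dropout is a round forecast.** The gap between 18.2% and 20% is finer than such a forecast can be. If each woman dropped out with probability 0.20, the number of completers per condition would vary with a standard deviation of √(55 × 0.80 × 0.20) = 2.97, so a shift of one lies well inside chance. This stands, and it is a good reason to call the point minor. It does not make the three figures agree.
- **The main analysis does not discard dropouts.** Under intention to treat with a mixed model over the four assessments of Table 1, a woman lost after a post-baseline assessment still contributes, so counting completers tends to understate the information available. This stands too. However, the plan itself enlarges the sample for attrition, and so treats 45 as the number needed afterwards. It also plans a per-protocol analysis, which does not gain from keeping every randomised woman, although following the protocol is not the same as not dropping out.
- **Nothing changes in practice.** One point of power alters no conclusion. This stands.

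Two stronger readings are tempting. A reader might infer that dropout was added to 45 instead of dividing by 0.80. But 45 × 1.20 = 54, not 55, and the article does not say how 55 was reached; rounding is as possible an origin. A reader might also infer that the trial is materially under-recruited. The shortfall of one completer per condition does not support that.

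**Conclusion.** The inconsistency is real and minor. From the article's own figures and without further assumptions, 55 per condition at 20% dropout gives 44 completers against a requirement of 45. Meeting 45 would take 57 per condition, and the planned number covers 18.2% dropout. The loss of about one percentage point of power rests on an assumed standardised difference of 0.5 and alpha of 0.05, and serves only to show the scale.

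This point does not bear on whether 45 per condition is the right requirement. Section 2.8 justifies that figure as "required to detect medium effects in comparison analyses", while section 2.1 describes a noninferiority design. That is a separate and weightier question, which correcting the dropout arithmetic would not answer.

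**What to change.** Restate the sentence in section 2.8 in one of two ways, leaving the sample at 110:

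- 110 participants (55 per condition) allow for about 18% dropout, keeping 45 per condition; or
- 110 participants (55 per condition) give 44 completers per condition at 20% dropout, with a note that this is one below the calculated 45.

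Either costs one sentence and no change to the design. Only if both 45 and 20% are to hold exactly should the minimum rise to 57 per condition. With 1:1 allocation that means 114 in total, since 113 cannot be split equally, at a cost of 114 − 110 = 4 more women.

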This article presents the study protocol for a blended CBT intervention combining face-to-face sessions with the online program Be a Mom for the treatment of PPD in the Portuguese context. In Portugal, the Be a Mom program was developed as a culturally sensitive web-based CBT intervention that is designed as a self-guided tool for the prevention of PPD. Preliminary evidence of Be a Mom’s pilot trial suggests its effectiveness in reducing depressive symptoms among women presenting early-onset PPD symptoms [30], thus supporting its potential as a PPD treatment tool integrated into a blended treatment protocol.

Therefore, we herein outline the protocol for a randomized controlled trial to examine the acceptability and efficacy of a blended CBT intervention for PPD treatment, considering postintervention and follow-up improvements in primary and secondary outcomes. It is expected that the blended CBT intervention will be as effective as treatment usually provided for PPD in decreasing depressive symptoms. In this study, we will evaluate the mediating role of psychological competences (self-compassion, emotion regulation, psychological flexibility) in treatment response. These mechanisms have been core psychological processes underlying the development of the Be a Mom program [31]. Moreover, previous studies have found that these psychological mechanisms were associated with improvements in depressive symptoms in the perinatal period [30,32,33]. We will also examine the moderator effect of characteristics of the patient (e.g., sociodemographic characteristics, motivation for therapy) and of the therapeutic process (e.g., therapeutic relationship, user’s satisfaction) in the efficacy of the blended intervention for PPD.

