#### 2.7.2. Primary Outcome

Changes in depressive symptoms, the primary outcome, will be measured with the Portuguese version of the Edinburgh Postnatal Depression Scale (EPDS) [40].The EPDS is a 10-item scale (e.g., “I have felt sad or miserable”) that assesses how women felt over the last seven days concerning several symptoms using an individualized four-point Likert scale (from 0 to 3). The total score can range between 0 and 30, and higher scores are indicative of more severe depressive symptoms. In Portuguese validation studies, a score of 10 or higher suggests the presence of clinically relevant depressive symptoms. The Portuguese version of EPDS showed good levels of internal consistency (Cronbach’s alpha = 0.85) and adequate validity [40].

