## 3. Discussion

Despite the existence of effective treatment, few women seek professional help to deal with their depressive symptoms in the postpartum period [7,8], indicating the need for a new and innovative format of treatment that can overcome help-seeking barriers. This study aims to evaluate the acceptability and effectiveness of a blended CBT intervention for the treatment of PPD in the Portuguese context by integrating face-to-face sessions with the web-based program Be a Mom.

To our knowledge, this will be the first study to develop a blended CBT treatment protocol for PPD. Blended Be a Mom benefits from both treatment formats, offering the flexibility, accessibility, and self-management of e-health tools as well as clinical support, increased motivation, and higher treatment intensity [21]. Moreover, it can potentially decrease the number of face-to-face sessions and reduce costs in healthcare systems. A blended CBT intervention can therefore increase help-seeking behaviors among women in the postpartum period by providing treatment that mitigates the impact of the identified barriers in professional help-seeking.

Existing studies have revealed that blended treatment for depression can be effective in reducing depressive symptoms and maintaining these gains over a period of six months [28]. Additionally, previous findings have shown that blended interventions are more effective compared to control groups without intervention (i.e., waiting lists) [24] and that it can be as effective as standard CBT treatments [29]. We expect that Blended Be a Mom will be as effective as TAU with regard to long-term effects on primary and secondary outcomes. The feasibility, acceptability, and usability of the blended intervention will be considered in addition to its cost-effectiveness.

Despite its advantages, there is still limited knowledge about the suitability of blended treatment for every patient [20]. Characteristics such as age, severity of symptoms, or the ability to use technology should be considered and further studied to optimize the effectiveness of blended interventions. The results of our study will provide insights into the processes underlying the treatment effects of blended intervention and the characteristics that moderate the effectiveness of blended intervention.

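### The trial is declared noninferiority, but section 2.8 sizes and analyses it to detect a difference, and no analysis named there tests noninferiority

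*Protocol article*

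**What the plan says.** Section 2.1 sets the design: "This study will be a two-arm, noninferiority randomized controlled trial (RCT) comparing blended CBT intervention for PPD" with TAU in primary healthcare centres. The Introduction gives the hypothesis: "It is expected that the blended CBT intervention will be as effective as treatment usually provided for PPD in decreasing depressive symptoms". The Discussion widens it: "We expect that Blended Be a Mom will be as effective as TAU with regard to long-term effects on primary and secondary outcomes".

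The primary outcome is fixed in section 2.7.2: "Changes in depressive symptoms, the primary outcome, will be measured with the Portuguese version of the Edinburgh Postnatal Depression Scale (EPDS"). Table 1 schedules it at baseline (T0), postintervention (T1) and two follow-ups (T2, T3).

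Section 2.8 contains the statistics. On size: "A sample of 45 women per condition is required to detect medium effects in comparison analyses, considering the primary outcome". With 20% dropout this becomes 55 per condition. On efficacy: "Linear mixed models will be conducted to determine the effects of the intervention over time (time × group interaction effects"), for primary and secondary outcomes alike. Further methods follow: "Other appropriate statistical analyses such as two-wave latent change score models, reliable change index, Chi-square tests, and within-group effect sizes will be performed", together with mediator and moderator analysis. Both intention-to-treat (ITT) and per-protocol (PP) analyses are planned.

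**The concern.** A noninferiority trial must reject the hypothesis that the new treatment is worse than the comparator by at least a stated amount. A time × group interaction test rejects the hypothesis that the arms do not differ in change. Its null hypothesis is close to the conclusion this trial hopes to reach. If the interaction is significant, the trial has found a difference. If it is not, the trial has only failed to find one, which happens more often when the sample is small or the outcome noisy.

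The sample-size sentence has the same orientation: it speaks of detecting an effect, not of excluding a loss. At stake is whether the trial, run and analysed as section 2.8 describes, can answer the question in section 2.1.

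**Working it through.** **1. Design against analysis**

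| Element | What the article fixes | Hypothesis it serves |
|---|---|---|
| Design (2.1) | Noninferiority to TAU | Exclude a relevant loss |
| Hypothesis (Introduction, Discussion) | Effectiveness equal to TAU | Exclude a relevant loss |
| Sample size (2.8) | 45 per arm to detect a medium effect | Detect a difference |
| Main efficacy analysis (2.8) | Time × group interaction | Detect a difference |
| Other named analyses (2.8) | Latent change scores, reliable change index, Chi-square, within-group effect sizes, mediation, moderation | None compares an estimate with a margin |
| Analysis sets (2.8) | ITT and PP | Suit noninferiority, but are not a test |

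**2. The plan's own figure**

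Section 2.8 gives no alpha, power or test family.
- A two-group t-test at d = 0.5 (two-sided 0.05, 80% power) needs 64 per arm.
- A repeated-measures ANOVA, between-group effect, f = 0.25, four measurements, correlation 0.6, 80% power, needs 90 in total, which is 45 per arm.

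So 45 can be reached under unstated inputs and is not shown to be wrong. Both routes are calculations for detecting a difference. With 20% dropout, 55 × 0.8 = 44 completers per arm.

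**3. What a non-significant interaction would mean**

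Assumptions, none stated in the article: n = 44 per arm, four visits, unit SD, compound symmetry with correlation rho, blended worse by d at T1, T2 and T3 and equal at T0, two-sided alpha 0.05.

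- Between-arm differences by visit: (0, d, d, d). Sum of squares about their mean: 0.75d², which is 0.0675 for d = 0.3 and 0.1875 for d = 0.5.
- Noncentrality: λ = (n/2) × 0.75d² / (1 − rho). It is the same for the omnibus test and for the contrast of T0 with the mean of T1 to T3.
- Denominator df: 3 × (2 × 44 − 2) = 258. Critical F: 2.64 on 3 df, 3.88 on 1 df.
- Example, d = 0.3 and rho = 0.5: λ = 22 × 0.0675 / 0.5 = 2.97. P(non-significant) = 0.73 on 3 df and 0.60 on 1 df.

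| True deficit | Test | rho 0.3 | rho 0.5 | rho 0.7 |
|---|---|---|---|---|
| 0.3 SD | 3-df omnibus | 0.80 | 0.73 | 0.57 |
| 0.3 SD | 1-df baseline versus post | 0.69 | 0.60 | 0.40 |
| 0.5 SD | 3-df omnibus | 0.50 | 0.34 | 0.12 |
| 0.5 SD | 1-df baseline versus post | 0.32 | 0.18 | 0.04 |

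If all 55 per arm were analysed, the 3-df figures at 0.3 SD would still be 0.76, 0.67 and 0.47. A plain two-group t-test with 45 per arm gives 0.71 at 0.3 SD and 0.35 at 0.5 SD.

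**4. What 45 per arm offers against a margin**

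Unadjusted comparison at one visit, true difference 0, one-sided 0.025:
- Half-width of the 95% CI: 1.987 × √(2/45) = 0.42 SD.
- Power ≈ Φ(margin / √(2/45) − 1.96). At a margin of 0.3 SD, Φ(1.423 − 1.96) = 0.30. At 0.5 SD, Φ(2.372 − 1.96) = 0.66, or 0.65 with the t distribution.
- n per arm for 80% power: 2 × (1.96 + 0.842)² / margin², which is 175 at 0.3 SD and 63 at 0.5 SD.
- Baseline adjustment helps: at 0.5 SD the 63 falls to 48 with a baseline correlation of 0.5, and to 33 with 0.7.

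The article gives neither a margin nor an EPDS SD, so these figures show a range only.

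**The case against.** The strongest reply is that this is detail a condensed article leaves to the full protocol or the SAP. A margin, a primary visit and a confidence-limit rule often sit there, and their absence here is not by itself a fault. That is accepted. The point does not rest on the absence. It rests on what section 2.8 does fix, a sizing aim and an efficacy analysis that both address a difference, in a trial declared as noninferiority. If a fuller document holds a noninferiority rule, section 2.8 still has to be reconciled with it.

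A second reply is that the mixed model is a suitable tool, since its time × group terms estimate between-arm differences in change and come with confidence intervals. That is right, and the fix keeps the model. What section 2.8 lacks is any step from those estimates to a noninferiority conclusion.

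Several stronger readings are tempting but unsupported:
- A reader might infer that a non-significant p-value will be reported as equal effectiveness. No such rule is written. It is an inference from the lack of any other route.
- The interaction is not the only efficacy analysis; section 2.8 names others. None of them tests noninferiority.
- The article does not say whether time is categorical or whether an omnibus test will be used, so the 3-df result is one case. The 1-df contrast has a direction and gives lower probabilities.
- The Discussion states an expectation for secondary outcomes, not a planned claim.
- How strong TAU turns out to be is a separate comparator question. Section 2.6.2 says that type and duration of therapy will be recorded.

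**Conclusion.** The conflict stands as a contradiction within the article: a noninferiority design and hypothesis, paired with a sample size and analyses framed to detect a difference. Followed as written, section 2.8 cannot deliver the conclusion that the trial is designed to reach.

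The size depends on the form of the test and the correlation between visits. Under the stated assumptions, a true deficit of 0.3 SD goes undetected with probability between 0.40 and 0.80, and one of 0.5 SD between 0.04 and 0.50. These are illustrations. Whether 0.3 or 0.5 SD would be an unacceptable loss depends on a margin that the article does not give. The logical point holds whatever the values.

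**What to change.** In section 2.8:

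1. Make the primary analysis the between-arm difference in EPDS (blended minus TAU) at one named visit, estimated from the planned mixed model.
2. Fix a noninferiority margin in EPDS points, with its justification, before any outcome data are seen.
3. Conclude noninferiority only if the upper limit of the two-sided 95% CI lies below that margin in both the ITT and the PP set, which are already planned.
4. Restate the sample-size sentence as the power that 45 per arm gives against that margin, with alpha, SD and any baseline adjustment stated.
5. Report the other visits and the secondary outcomes as estimates with confidence intervals, without a claim of equal effectiveness.

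The data, visits and model stay the same. The cost is one decision on the margin and a stated power that may be less favourable than the present sentence suggests: about 30% at a margin of 0.3 SD and about 65% at 0.5 SD without adjustment, and higher with baseline adjustment.
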